### Secondary outcome

The incidence of organ dysfunction and organ function were evaluated according to the modified Marshall score.Complication: The complication rate mainly includes short-term and long-term complication rates, among which short-term complications include bleeding, gastrointestinal perforation, and pancreatic leakage. Long-term complications include incisional hernia, pancreatic endocrine and exocrine dysfunction, chronic pancreatitis, and portal hypertension. Pancreatic endocrine dysfunction was defined as HbA1c ≥ 6.5% (48 mmol/mol) and/or FPG ≥ 126 mg/dl (7.0 mmol/l) 3 months after diagnosis or pancreatitis. Pancreatic exocrine dysfunction was determined in a variety of ways including direct pancreatic function testing, measurement of fecal elastase or fecal fat levels (72 h fecal fat excretion > 7 g/d) and need for oral pancreatic enzyme replacement therapy. Chronic pancreatitis was defined as repeated upper abdominal pain; abnormal serum or urine pancreatic enzyme concentrations (lipase or amylase activity 2–3 times above the upper limit of normal); abnormal exocrine function (stool elastase < 200 µg/g) while the endosonography/CT/MRI imaging shows dilated main duct and side branches, intraductal and parenchymal calcifications[10, 11].The number of surgical procedures which includes PCD and the total number of operations.Mortality: The incidence of in-hospital death and deaths within 90 days of discharge.The length of hospital stays, the length of intensive care unit (ICU) stay, and hospitalization costs.Changes in inflammatory markers, including white blood cell (WBC), interleukin-6 (IL-6), C-reactive protein (CRP), and procalcitonin (PCT)

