**Methods:**

This is an ongoing, single-center, randomized controlled trial of patients with IPN. The total sample size required for the trial (May 2021–December 2023) is approximately 128 patients. Patients will be randomly assigned to either an experimental group (One-step) or a control group (Step-up) at a ratio of 1:1 using the block randomization method. We used the case report forms and electronic data capture systems to obtain demographic information, preoperative laboratory examination, auxiliary examination results, surgery data, postoperative recovery outcomes, and follow-up outcomes. The patients will be followed up for 2 years after surgery. The primary endpoint is a composite endpoint, consisting of mortality and severe complications. The secondary endpoints include the incidence of organ dysfunction, the number of surgical procedures, mortality (the incidence of death in hospital and deaths within 30 days of discharge), hospital stay, intensive care unit stay, hospitalization costs, perioperative inflammatory marker changes, and short-and long-term complications.

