#### Allocation concealment mechanism

Patients will be randomly assigned to the experimental group (One-step approach) and the control group (Step-up approach) at a ratio of 1:1 using the block randomization method.

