### Data collection

Clinical data of enrolled patients will require collection through a case report form (CRF) and the electronic data capture (EDC) system. Every month, clinical research associates (CRAs) monitor the electronic database to guarantee data quality when the clinical research coordinator (CRC) enters the clinical data into the EDC system from the CRF.

The CRF includes the following data: (1) Demographic information: sex, age, body mass index, concomitant disease, and medication use; (2) Perioperative laboratory examination: results of routine blood tests, biochemical tests, serum CRP test, PCT, IL-6, and arterial blood gas tests; (3) Auxiliary examination: all enrolled patients will undergo abdominal enhanced CT scans; (4) Surgery data: operation date, operation time, number of operations, blood loss, surgical methods, and intraoperative complications; and (5) Postoperative recovery outcomes: hospital stay, length of ICU stay, organ dysfunction, perioperative blood pressure, and heart rate, hospitalization cost, short-term and long-term postoperative complications, and death (Table 3).

**Table 3 Tab3:** Checklist for the collection of necessary clinical data and follow-up scheme for enrolled patients with IPN

	Baseline		Post-operation				Follow-up					
	Pre-operation	Operation	POD 1	POD 3	POD 7	POD 30	3 months	6 months	9 months	12 months	18 months	24 months
Inclusion/exclusion criteria	×											
Informed consent	×											
Allocation	×											
Demographic information	×											
Laboratory examination	×		×	×	×	×	×	×	×	×	×	×
Auxiliary examination	×						×	×	×	×	×	×
Surgical data		×										
Postoperative recovery outcomes			×	×	×	×						
Physical examination	×						×	×	×	×	×	×

× indicates the need to collect clinical data

POD, postoperative day

The important privacy information of patients will be replaced with statistical codes or numbers, then CRC will transfer the data from CRFs to the EDC system (https://edc.trialdata.cn/Member/Login), and all clinical data will be analyzed anonymously via the EDC system. Detailed results will be openly shared with the permission of the corresponding author at the end of the study.

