### Sample size

The sample size was calculated using PASS 11.0 (NCSS Statistical and Data Analysis, USA) software and was estimated based on the results of our center’s previous research and published literature. According to our previous studies and domestic and foreign reports, the incidence of a mixed endpoint is approximately 20% for the “One-step” approach and approximately 45% for the “Step-up” approach [8]. Using a one-sided test, the α value was equal to 0.05, and the statistical power was 80%. The withdrawal rate was expected to be 20% during the study period. Thus, this study requires at least 128 patients, with 64 patients each group.

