### Statistical analyses

The results of this trial for primary outcomes will be analyzed based on both the intention-to-treat protocol and per-protocol datasets. SAS 9.2 software (SAS Institute Inc.) was used to generate the randomization sequence. Statistical analyses will be performed with SPSS 21.0 (IBM Corp., Armonk, NY, USA) statistical software. The continuous variables with normal distributions will be described as mean ± standard deviation, and an independent sample *t-test* will be used for difference tests. The continuous variables with non-normal distributions will be described by the median (IQR), and the Mann–Whitney U test will be used for the difference tests. The Chi-square test or Fisher’s exact test will be used for categorical data. The Chi-square test or Fisher’s exact test will be used to assess adverse events. The Kaplan–Meier method will be used to calculate survival analysis. The log-rank test will be used to compare the complication rate between the two groups, and *P* values < 0.05 will be considered statistically significant.

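### Inflammatory marker changes are compared by unadjusted t-test or Mann-Whitney although pre-operative values are collected: valid, but less precise than a baseline-adjusted analysis

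*Protocol article*

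**What the plan says.** The protocol article, Secondary outcome, ends its list with "Changes in inflammatory markers, including white blood cell (WBC), interleukin-6 (IL-6), C-reactive protein (CRP), and procalcitonin (PCT". It does not say whether this means baseline-subtracted values or the values at successive visits, and it names no key day.

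Under Statistical analyses, for normally distributed continuous variables "an independent sample *t-test* will be used for difference tests"; for the others "the Mann–Whitney U test will be used for the difference tests". The rule is general and does not name the markers, but they are continuous and no other rule covers them. ANCOVA, regression and mixed models appear nowhere in the article.

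The baseline values exist. Data collection lists "Perioperative laboratory examination: results of routine blood tests, biochemical tests, serum CRP test, PCT, IL-6, and arterial blood gas tests", and Table 3 marks laboratory examination at pre-operation, on postoperative days 1, 3, 7 and 30, and at every follow-up visit. The abstract also mentions "preoperative laboratory examination".

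Allocation is "at a ratio of 1:1 using the block randomization method". No stratification by a baseline marker is described.

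**The concern.** When an outcome is also measured before treatment, that measurement usually explains part of the later variation between patients. A two-sample test leaves this part in the error term. The change score uses the baseline, but with a fixed weight of one, which is generally not the best weight. A test on follow-up values ignores the baseline altogether. ANCOVA estimates the weight from the data and, with equal SDs and r between 0 and 1, is more precise than either.

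At stake is the precision with which the trial describes the biological response to the two strategies. The markers were not used to size the trial, so lost precision here is not made up elsewhere.

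**Working it through.** **The plan's own figure.** The only stated sample size is for the primary composite: 64 per group, 128 in total. The inputs are in Sample size: "the incidence of a mixed endpoint is approximately 20% for the “One-step” approach and approximately 45% for the “Step-up” approach", and "Using a one-sided test, the α value was equal to 0.05, and the statistical power was 80"%, with 20% withdrawal. The one-sided two-proportion formula with continuity correction gives 51 per arm; 51/0.8 = 63.75, rounded up to 64, so 128. The figure reproduces. It does not depend on the markers. It does supply 51 evaluable patients per arm for the checks below.

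**Assumptions.** The documents give no SD and no correlation for any marker. I assume equal SDs (s) at baseline and follow-up and a correlation r of 0.2, 0.5 or 0.7.

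**Variances per patient, in units of s².**
- Change score: 2(1-r)
- Follow-up value alone: 1
- ANCOVA: 1-r²

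ANCOVA relative to change score: (1-r²)/[2(1-r)] = (1+r)/2. ANCOVA relative to follow-up value: 1-r².

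| r | Change score | Follow-up | ANCOVA | ANCOVA / change | ANCOVA / follow-up |
|---|---|---|---|---|---|
| 0.2 | 1.60 | 1 | 0.96 | 0.60 | 0.96 |
| 0.5 | 1.00 | 1 | 0.75 | 0.75 | 0.75 |
| 0.7 | 0.60 | 1 | 0.51 | 0.85 | 0.51 |

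The saving is therefore 40%, 25% and 15% of the variance if change scores are tested, and 4%, 25% and 49% if follow-up values are tested. The two readings run in opposite directions as r rises.

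**In terms of power.** Take 51 per arm and a two-sided 0.05 level (my assumption for the markers), and an effect that ANCOVA detects with 80% power. At r = 0.5 this effect is (1.960+0.842) × √(2/51) × √0.75 = 0.48 SD. The unadjusted t-test then has this power:

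| r | t-test on change | t-test on follow-up value |
|---|---|---|
| 0.2 | 58% | 78% |
| 0.5 | 68% | 68% |
| 0.7 | 73% | 52% |

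**Simulation.** With 5000 runs of normal data at r = 0.5, power was 67% for the t-test on change, 65% for Mann-Whitney on change and 79% for ANCOVA. The empirical standard errors were 0.199 SD (change) and 0.173 SD (ANCOVA). The mean estimates were 0.483 and 0.484 against a true 0.480, so neither method is biased.

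**Chance imbalance.** The baseline difference between arms has an SD of √(2/64) = 0.18 marker SD at 64 per arm, or √(2/51) = 0.20 at 51. An imbalance of 0.2 SD moves the change-score estimate by -0.2(1-r): -0.16 SD at r = 0.2, -0.10 at 0.5 and -0.06 at 0.7. It moves the follow-up comparison by +0.2r: 0.04, 0.10 and 0.14. ANCOVA removes this shift in expectation. The standard error of the unadjusted test already allows for it.

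**The case against.** The strongest reply is that the criticised analysis is inferred. The outcome is given in a phrase, the test rule is generic, and a condensed article commonly leaves the model for a repeated laboratory measure to an analysis plan that is not shown. It stands that the article does not define the quantity analysed. But it does not leave the test open either: it names two, both unadjusted, and precision is lost on either reading.

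Three stronger readings are tempting and are not supported.

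- A reader might infer a single saving of 15-40%. That range holds only for change scores with equal SDs and r between 0.2 and 0.7. On follow-up values the saving at r = 0.2 is 4%. The documents give neither r nor the SDs, and equal spread before treatment and a month later is not shown.
- A reader might infer that the comparison is biased, because chance imbalance could create or mask an effect. Under 1:1 randomization this is ordinary sampling error, already in the standard error. The simulation shows no bias.
- A reader might infer that skewness makes raw change scores worse still. The documents give no distribution for these markers. Skewed values would go to the Mann-Whitney test under the article's own rule, and the variance ratios above do not apply directly to a rank test.

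One further objection stands in full: a model by postoperative day is not ready to use as the article is written. Step-up patients have percutaneous drainage first, and debridement follows only if infection symptoms persist at 48 h (“Step-up” section and Perioperative treatment). Some may never have debridement, so postoperative day has no evident common origin across arms.

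**Conclusion.** The point holds as one of efficiency. The stated tests are valid under randomization but discard information that the trial already collects. The ANCOVA variance is 0.60 to 0.85 of the change-score variance, or 0.96 to 0.51 of the follow-up variance, as r goes from 0.2 to 0.7. These figures rest on an assumed r, equal SDs and roughly normal values on the scale analysed. What does not depend on the exact r is the direction: for any r between 0 and 1, adjustment improves on both unadjusted t-test analyses.

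The importance is minor. The markers are one secondary outcome among several, and neither the primary analysis nor the sample size is touched.

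**What to change.** State that each marker will be analysed by ANCOVA at a named time point, or by a repeated-measures model over the scheduled visits, with arm as factor and the pre-treatment value as covariate. Use the log scale for outcome and covariate if the values are skewed. Report the adjusted difference, or the ratio of geometric means, with a 95% CI.

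Count time from an origin that both arms share, for example randomization or first intervention, and say how the postoperative-day visits in Table 3 map onto it for Step-up patients. This needs settling before a model over visits is written down.

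The cost is a short passage of analysis text plus the decision on the time origin. The adjustment needs no new measurement and no extra patients. If visits have been dated only from debridement, the interval from the common origin must be derived from recorded dates.

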### Interventions

In this study, we compare the surgical treatment for IPN which include “One-step” and “Step-up” minimally invasive pancreatic necrotic tissue debridement. Although, the endoscopic transmural (transgastric or transduodenal) necrosectomy was also considered as an effective treatment for IPN [12], it was not routinely used in this study.

### “One-step” minimally invasive pancreatic necrotic tissue debridement

This method is a direct, minimally invasive surgery, omitting one of the surgical procedures of percutaneous catheter drainage (PCD). According to the preoperative imaging examination, “One-step” minimally invasive pancreatic necrotic tissue debridement can be performed via the omentum sac or retroperitoneal approach.

Since the IPN partition is directly related to the surgical approach, clinicians need to determine the type of IPN partition by abdominal CT scan prior to “One-step” minimally invasive pancreatic necrotic tissue debridement. The surgical procedures for the two different surgical approaches and IPN partition are described in Table 2.

**Table 2 Tab2:** The IPN distribution and the selection of surgical approach

Region	IPN distribution	Surgical approach
I	Peripancreatic area†	Median abdominal approach
*II*		
IIa	Left posterior colon area‡	Median abdominal approach or left retroperitoneal approach was used to drain the head of the pancreas
IIb	Left pelvic area§	Left retroperitoneal approach was used to drain the caudal side of the pancreas
III	Right posterior colon area¶	Right retroperitoneal approach

^†^ Peripancreatic area includes intraomentum, pancreas, transverse colon, and mesentery root, perisplenic, and left subdiaphragmatic area

^‡^ Left posterior colon area includes left posterior colonic space, the anterior and posterior space of left pararenal, and the perirenal space, but the pelvis cavity is not involved

^§^ Left pelvic area includes the anterior and posterior space of rectum

^¶^ Right posterior colon area includes the posterior space of duodenum, posterior space of right colon, anterior and posterior space of right pararenal, and right perirenal space

#### Omentum sac surgical approach

(1) Incision selection: The preoperative CT scan will be carefully evaluated, and the boundary of the peripancreatic abscess will typically be marked by the xiphoid process or umbilicus. The incision should be selected in the midline nearest to the abscess, and the stomach and transverse colon should be avoided as far as possible. The incision length is usually approximately 5 cm. (2) Passage is established through the omental sac: After entering the abdominal cavity, the gastrocolic ligament is incised below the vascular arch of the gastroepiploic artery. Bleeding caused by injury to the gastroepiploic vessels must be thoroughly sutured to avoid postoperative bleeding in the abdominal cavity or the omental sac. The gastrocolic ligament and parietal peritoneum are sutured around the circumference to establish access and protect the abdominal cavity from pus inflow. The location of the abscess cavity will be determined by fine-needle puncture (application of intraoperative ultrasound positioning) and bluntly separate into the abscess cavity. (3) Video-assisted pancreatic necrotic tissue debridement: After the tissue is collected for bacterial culture, pus is absorbed as much as possible, and the abscess cavity is observed through video equipment. Under video guidance, the necrotic tissue is removed with an aspirator, oval forceps, or laparoscopic instrument, blood vessels are carefully protected, and immature necrotic tissues are preserved. (4) Place drainage tube: The drainage tube is placed under laparoscopy and the location and number of placements depend on the location and size of the abscess. It is recommended to use a 30–36Fr three-chamber drainage tube to reduce the risk of blockage.

#### Retroperitoneal surgical approach

(1) Incision selection: Carefully evaluation will be made of the results of the CT scan before surgery, and the midaxillary line is usually used as the body surface marker. The incision should be selected near the midaxillary line closest to the abscess (surgery can be performed through the left or right midaxillary line) while avoiding the ascending colon, duodenum, and descending colon as much as possible. The incision length is usually approximately 5 cm. (2) The retroperitoneal passage will be established: Incise the skin, subcutaneous tissue, and abdominal wall muscle, and hemostasis of the abdominal wall muscle should be thorough to avoid postoperative wound bleeding. After entering the peritoneum through the retrocolic space, the abscess cavity will be determined by fine-needle puncture and then bluntly separated into the abscess cavity. Video-assisted pancreatic necrotic tissue debridement and drainage tube placement are the same as those in the omentum sac surgical approach. Surgery can be performed through the left and right midaxillary line or bilateral approaches. The first operation is usually performed under general anesthesia with tracheal intubation or laryngeal mask, and the second operation may be performed under local anesthesia depending on the abscess and the general condition.

### “Step-up” minimally invasive pancreatic necrotic tissue debridement

“Step-up” minimally invasive pancreatic necrotic tissue debridement which uses PCD as the initial treatment option for IPN. The retroperitoneal approach is the preferred approach for PCD treatment under the guidance of B-ultrasound or abdominal CT scans. “Step-up” minimally invasive surgery should be considered if the patient’s infection symptoms do not resolve within 48 h following PCD treatment. The surgical approach is the same as the “One-step,” and the surgical approach was retroperitoneal or omentum sac, depending upon the path of the PCD drainage tube and preoperative imaging examination. If there is residual infection in the abdominal cavity after minimally invasive surgery, PCD treatment is preferred. Open surgery is only used as the last rescue measure after the failure of minimally invasive surgery.

### Perioperative treatment for enrolled patients

For patients who received “One-step” minimally invasive pancreatic necrotic tissue debridement, clinicians must provide symptom-based treatment, such as electrocardiograph monitoring, antibiotics, proton pump inhibitors, analgesics, octreotide, and nutrition support. Routine blood tests, serum CRP, PCT, IL-6, and arterial blood gas tests will be used to monitor delayed bleeding, incision, and/or abdominal infection after surgery. After the recovery of gastrointestinal function, a semi-liquid diet can be gradually administered until a normal diet is resumed. In addition, it is also necessary to pay attention to the characteristics of the drainage fluid in the abdominal drainage tube and be alert to delayed abdominal hemorrhage. When the amount of drainage fluid in the abdominal drainage tube is gradually reduced and the characteristics of the drainage fluid are clear, the drainage tube can be removed gradually. The patients can then be discharged from the hospital.

For patients who received “Step-up” minimally invasive pancreatic necrotic tissue debridement, clinicians provide electrocardiograph monitoring, antibiotics, proton pump inhibitors, analgesics, octreotide, and nutrition support after receiving PCD therapy. Routine blood tests, serum CRP, PCT, IL-6, and arterial blood gas tests are continued to monitor the abdominal infection. If the patient’s infection symptoms are resolved, the current therapies will be continued until normal status is achieved. If the patient’s infection symptoms are not relieved within 48 h of PCD treatment, they will undergo minimally invasive pancreatic necrotic tissue debridement. The postoperative treatment is the same as the “One-step” approach.

### Assignment of intervention for allocation

#### Sequence generation

To ensure the matching of clinical data between the two groups, the participants will be randomly assigned to the experimental group and the control group by block randomization. SAS 9.2 software (SAS Institute Inc., NCSU, USA) will be used to generate the randomization sequence and each patient will be assigned a numeric randomization code.

#### Allocation concealment mechanism

Patients will be randomly assigned to the experimental group (One-step approach) and the control group (Step-up approach) at a ratio of 1:1 using the block randomization method.

### Implementation

The Contract Research Organization in Xuan Wu Hospital will generate the allocation sequence, enroll participants, and assign participants to interventions.

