### Assignment of interventions for blinding

The study is a single-blind trial in which the patients will be blinded to their grouping. However, the surgeon will provide the corresponding surgical treatments according to the grouping of patients. After patients are discharged from the hospital, clinicians will send the surgical methods in the form of medical records through the Email.

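### One body generates the sequence, enrols and assigns, no concealment step is named, and plain blocks are credited with matching the arms; separately, pre-operative marker values are left out of the listed tests.

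*Protocol article*

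**What the plan says.** All places are in the protocol article.

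- **Implementation:** a contract research organisation in the trial hospital "will generate the allocation sequence, enroll participants, and assign participants to interventions".
- **Allocation concealment mechanism:** the whole section says that patients are randomised to the two arms "at a ratio of 1:1 using the block randomization method".
- **Sequence generation:** the purpose given for the blocks is "To ensure the matching of clinical data between the two groups". The software is named. No stratification factor is named, and no block size is given.
- **Assignment of interventions for blinding:** only patients are blinded; "the surgeon will provide the corresponding surgical treatments according to the grouping of patients".
- **Study design and setting:** there is one centre, and randomisation follows consent.
- **Inclusion criteria:** these include a stable general condition without multiple organ failure, and being fit for video-assisted debridement.
- **Secondary outcome and Statistical analyses:** changes in four inflammatory markers are a secondary outcome. For continuous variables the t-test "will be used for difference tests", with Mann–Whitney if the distribution is not normal. No baseline covariate enters any listed test, although Table 3 schedules laboratory examination before operation.

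**The concern.** Concealment means that whoever decides on a patient's entry cannot know the next assignment. Blocking does not provide this. It restricts the sequence, and it makes the sequence easier to predict. The section headed for concealment describes only the blocks, and the next section places list-making, enrolment and assignment in one body.

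The setting makes this matter. Some entry criteria leave room for judgement. The Discussion holds that patients in good condition may not need catheter drainage first, and the abstract already credits One-step with better efficacy and safety. If the next assignment were known, fitter patients could be steered to One-step, and analysis cannot reliably repair that bias.

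The matching phrase is a separate error of fact. It promises prognostic balance that the described procedure cannot deliver.

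The marker analysis raises a third and smaller matter: information already collected before surgery is not used, so precision is lost.

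**Working it through.** **1. The plan's own figure.** Inputs from Sample size: 20% against 45%, one-sided α 0.05, power 80%, withdrawal 20%.

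- Uncorrected: n = [1.645·√(2·0.325·0.675) + 0.842·√(0.20·0.80 + 0.45·0.55)]² / 0.25² ≈ 42.3 per arm.
- With continuity correction: (n/4)·[1 + √(1 + 4/(n·0.25))]² ≈ 50.02, so 51 per arm.
- With withdrawal: 51/0.80 = 63.75, so 64 per arm and 128 in all.

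The stated 128 is reproduced. It does not depend on this point.

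**2. How predictable fixed blocks would be.** The block size is not stated, so the sizes below are assumptions. The observer is assumed to know the block size and every past assignment. For blocks of 4 there are 6 sequences and 24 positions. AABB and BBAA each fix their last two positions, and the other four sequences fix only the last, so (2·2 + 4·1)/24 = 8/24 = 1/3. Full enumeration gives:

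| Block size (assumed) | Known with certainty | Of 128 | Best-guess hit rate |
|---|---|---|---|
| 2 | 50% | 64 | 75% |
| 4 | 33% | 43 | 71% |
| 6 | 25% | 32 | 68% |
| 8 | 20% | 26 | 67% |

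Anyone who holds the list and also enrols would know 100%, whatever the block size.

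**3. What unstratified blocks balance.** They fix the arm totals at the end of each block and leave baseline factors to chance. Take a binary factor with assumed prevalence 30% and 64 per arm. The SD of the between-arm difference is √(2·0.3·0.7/64) = 0.081. The exact binomial probability of a gap of 10 points or more is 21%. At assumed prevalence 50% the SD is 0.088 and the probability 25%. With 51 per arm the two probabilities are 23% and 28%. Matching of clinical data is therefore not ensured.

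**4. Gain from using the pre-operative marker value.** Assume equal variance σ² before and after surgery and correlation r.

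- Raw change score: variance 2σ²(1 − r).
- ANCOVA: variance σ²(1 − r²).
- Ratio: (1 − r²)/[2(1 − r)] = (1 + r)/2.

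| r (assumed) | ANCOVA ÷ change score, (1 + r)/2 | ANCOVA ÷ follow-up value alone, 1 − r² |
|---|---|---|
| 0.3 | 0.65 | 0.91 |
| 0.5 | 0.75 | 0.75 |
| 0.6 | 0.80 | 0.64 |

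The plan does not say whether the change or the follow-up value is tested, so both comparisons are shown. ANCOVA has the smaller variance in each.

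**The case against.** The strongest reply is that nothing here shows allocation being foreseen, and that is correct. One organisation doing three tasks need not mean one person doing them. Separate custody of the list may be set out in a full protocol or operating procedure that a journal article condenses. The block size is not given, and withholding it is good practice. A surgeon is said to know the arm of the patients he or she treats, not the whole sequence; there are three surgeons, and enrolment is not assigned to them. The article already places randomisation after consent. A reader might infer that past assignments do reveal the next one, but the documents do not support that.

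What survives is narrower. The combined roles are a positive statement, not an omission, and the article gives concealment its own section but fills it with something that is not concealment.

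A reader might also infer that chance imbalance makes the unadjusted tests misleading. It does not. With sound concealment, the type I error rate already allows for chance imbalance, and what is lost is precision. The size is also modest: if a factor raised risk by 30 points (assumption), a 10-point imbalance would move the risk difference by 0.10 × 0.30 = 3 points, against a planned 25. Adjustment of the primary outcome may also sit in an analysis plan that is not shown.

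Finally, the marker gain concerns one secondary outcome and rests on assumed correlations. That is true, but the article names the tests for continuous variables, and a better method is available from data it already collects.

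**Conclusion.** The point holds in three parts of different weight.

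- **Concealment:** the plan gives sequence generation, enrolment and assignment to one body and names no mechanism. With one centre, unblinded surgeons and judgement in eligibility, this is a risk of foreseen allocation, not an established fault. The 20% to 50% of assignments known with certainty applies only if block sizes are fixed, lie between 2 and 8, and are known together with all past assignments.
- **Matching:** the phrase is wrong as it stands. Blocks without stratification balance numbers only.
- **Markers:** baseline adjustment would improve precision and corrects no bias. Against raw change scores the variance ratio is 0.65 to 0.80 for r from 0.3 to 0.6, given equal variances before and after surgery.

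None of this alters the sample size, and none of it makes the listed tests invalid.

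**What to change.** For patients still to be randomised:

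1. Have a statistician independent of enrolment generate and hold the list, with varying block sizes that are not disclosed to site staff. Staff who enrol have no access to it.
2. Release each assignment only after consent and eligibility are recorded, either electronically or by sealed opaque envelopes. State this in the concealment section.
3. Delete the matching phrase, or say that blocks keep group sizes equal.

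For patients already randomised, document who held the list and how assignments were concealed.

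Separately, analyse the inflammatory markers, on the log scale where skewed, by ANCOVA or a repeated-measures model with the pre-operative value as covariate, in place of the unadjusted t-test or Mann–Whitney test. As an option, adjust the primary risk difference for age, which is collected, and for the modified Marshall status assessed at eligibility. The case report form lists organ dysfunction only among postoperative outcomes, so the baseline status would need to be recorded.

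The cost is a small amendment with ethics review, set-up of the release procedure (the data capture system is described for data entry and monitoring, with no randomisation function mentioned), and a little more analysis work. No patients are added, and the total stays at 128.
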